## Introduction

A prolonged first episode of psychosis (FEP) without adequate treatment is a consistent predictor of poor clinical and functional outcomes [1], poor health outcomes [2], and significant economic burden [3]. Individuals with psychotic disorders can experience positive symptoms (e.g., delusions and hallucinations), negative symptoms (e.g., reduced motivation, difficulty expressing emotions) [4], and cognitive impairments that may significantly impact daily functioning [1].

Team-based “coordinated specialty care” (CSC) [5] for early psychosis (EP) has established effectiveness in promoting clinical and functional recovery [6]. This intervention includes case management and coordination, ongoing psychiatric and/or medical assessments and treatment, service user and support person psychoeducation and psychotherapy, educational and vocational support, and relapse prevention. Recent state and federal initiatives have led to the rapid and widespread dissemination of CSC across the United States, such as New York [7] and Texas [8]. However, CSC program development has been disconnected both across and within states and specific clinical services offered can vary as a result. For example, CSC programs in California have developed locally within specific health systems and counties and with little coordination with each other. This lack of state and national coordination and data infrastructure limits the capacity for data-based innovation, accelerated dissemination of best practices, and broad-scale evaluation [9]. To address this, EPI-CAL proposed to develop a learning health care network (LHCN) of EP programs across California.

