#### Program fidelity

In addition to the program-level data described here, we also collect project data via fidelity assessments, program surveys, and the program level core assessment battery (PL-CAB). Each program completes a fidelity assessment to determine the components of coordinated specialty care (CSC) provided using the First Episode Psychosis Services Fidelity Scale (FEPS-FS) [51], a standardized measure of fidelity to EP program best practices. Similar to the fidelity assessments, program surveys and the PL-CAB assess various components offered through the CSC program, program census, and staffing. The data from these other sources may also be used to inform the analysis of the program-level data.

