Through the qualitative work that was completed in the first phase of this project [24], a variety of key outcomes were identified by our program, service users, and support person workgroups. Psychiatric symptoms, quality of life, and functioning were prioritized as key outcomes by all types of respondents and our analysis will center on these domains. When examining group-level differences, it is important to note that there is not a “Beehive” and “not Beehive” group of service users; all service users are assigned to the Beehive group and thus no analysis can examine the effect of Beehive use in treatment compared to a typical control group. Instead, to assess the impact of utilizing MBC in an EP LHCN (Aim 3), we will analyze a dataset consisting of one record per service user per follow-up assessment timepoint and outcomes expressed as within-person change scores from baseline (for continuous measures) or as count or binary outcomes. For count or binary outcome data, the corresponding baseline value of the outcome will be included as a person-level covariate, when appropriate. Outcomes will be measured by the MCSI, personal wellbeing index (PWI), and functioning measures (Global Functioning Social and Role Scales (GF: S and GF: R) or Mental Illness Research, Education, and Clinical Center (MIRECC) version of the Global Assessment of Functioning (GAF) scale) for each of the six-monthly assessment timepoints during the first 24 months. Continuous outcomes will be transformed into within-person change scores from the baseline assessment for each follow-up assessment. Data are structured hierarchically; there is nesting of measurements from service users, who are nested within clinicians within EP programs. Therefore, for continuous, binary, and count outcomes, generalized linear mixed models will be used to estimate the adjusted effects of exposures on the key outcomes of interest, adjusting for a parsimonious set of other clinician- and service user-level covariates. Random effects will be specified for sites, with additional effects specified for clinician and service users’ contribution to the model fit, according to the Schwarz Information Criterion.

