A key operationalization of the exposure indicator will be based on a composite indicator for any review of the service users’ completed surveys. In particular, this variable will be scored a 1 for a given service user in a given follow-up assessment if the treatment team lead reviewed the service users’ completed survey data. The comparison groups are defined by clinician metrics from Beehive aggregated over the 6-, 12- and 18-month assessment period, and the primary analysis is based on a composite indicator for any review of the service users’ survey data by the treatment team lead. We will also assess timepoint-specific changes in psychotic symptom severity for each of the half-yearly assessment timepoints during the first 24 months, with the primary analysis based on a time-varying indicator for any endorsement of “impact on treatment plan” on the in-app queries as a time-varying independent variable.

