While collecting a harmonized dataset of key outcome measures is a major goal of EPI-CAL LHCN, the heterogeneity across programs enables detailed analysis of specific program elements that lead to program success and improved treatment outcomes for service users within the network. Specific program elements will be evaluated by conducting a fidelity assessment with each program. In addition to program elements, we will also examine if treatment outcomes vary based on clinician’s use of data in care. For example, we will examine treatment outcome differences across service users whose treatment team lead examines the service user-level data available in Beehive and whether they incorporate this data into care decisions. We will include relevant clinician metrics in our analyses of treatment outcomes, which include clinician demographic information collected at registration, such as degree level, and years working with this specific population.

Beyond establishing the California Learning Health Care Network of EP programs, EPI-CAL will provide a harmonized dataset to the EPINET initiative for the purpose of advancing early psychosis care, improving recovery outcomes, and scientific discovery. The contribution of outcomes data from the California network to the national level via EPINET will improve the development of EP care, early intervention, and provide even greater opportunities for large-scale evaluation and research of EP care.

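### The Aim 3 model leaves the effect of survey review open to confounding between programs, because a random site intercept does not separate within-program from between-program contrasts

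*Protocol article*

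**What the plan says.** The Data analysis section of the protocol article says Aim 3 has no conventional control group. The statement, cut here before its last three words, reads "all service users are assigned to the Beehive group and thus no analysis can examine the effect of Beehive use in treatment compared to a". The contrast is observational: "the primary analysis is based on a composite indicator for any review of the service users’ survey data by the treatment team lead".

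The generalized linear mixed model is described as "adjusting for a parsimonious set of other clinician- and service user-level covariates. Random effects will be specified for sites". Effects for clinician and service user are then added or left out by the Schwarz criterion. No program-level covariate is named, and no within-program contrast is specified.

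Elsewhere the article describes a varied network:

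- The Introduction says "CSC program development has been disconnected both across and within states and specific clinical services offered can vary as a result", and adds that the participating clinics take different approaches to coordinated specialty care (CSC).
- The Discussion says "the heterogeneity across programs enables detailed analysis of specific program elements that lead to program success and improved treatment outcomes".
- The section on outcome measures plans to draw interviewees from clinics with high and with low Beehive adoption.
- The Program fidelity section says that every program completes the FEPS-FS, and that program surveys and the PL-CAB record components, census and staffing. On their use it says only "The data from these other sources may also be used to inform the analysis of the program-level data".

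**The concern.** A random intercept allows for correlation among service users of one program. It does not adjust for program in the way that a fixed effect does. It assumes that the program effect is independent of the covariates in the model, including review. If programs with better trajectories also review more, part of the difference between programs is absorbed into the review coefficient.

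The article anticipates differences between programs in care, in the elements that drive outcome and in use of the platform. These are the ingredients of a path from program to review and from program to outcome. What it does not establish is that the two are correlated.

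At stake is the reading of Aim 3. The Objectives speak of association, but the Data analysis section speaks of the impact of measurement-based care and of adjusted effects. A positive coefficient would be read as support for review, when part of it could be a difference between programs.

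**Working it through.** **Inputs from the article.** About 800 service users (500 FEP plus 300 CHR, Sample size section); a binary review indicator; a random site effect; no program-level covariate. The article gives no ICC, number of programs, effect size or SD for Aim 3, so there is no stated figure to reproduce.

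**Assumed inputs.** 12 to 20 programs; 400 to 800 service users with follow-up; ICC of the change score 0.02 to 0.10; correlation ρ between program quality and review of 0, 0.3 or 0.7; one record per person; true effect of review zero; outcome SD 1.

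**Formula.** With K equal programs of m = N/K people, the random-intercept estimate is approximately

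β = (1 − w)·β_within + w·β_between, where

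- w = θ·S_B / (S_W + θ·S_B)
- θ = (1 − ICC) / [(1 − ICC) + m·ICC]
- S_B is the variance of program review rates, and S_W = 0.25 − S_B when half of all surveys are reviewed.

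With no true effect, β_within = 0. The spurious between-program slope is ρ·√ICC / √S_B.

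**One case by hand.** K = 20, N = 800, m = 40, ICC = 0.05, SD of program review rates 0.21.

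- S_B = 0.21² = 0.0441; S_W = 0.25 − 0.0441 = 0.2059
- θ = 0.95 / (0.95 + 40 × 0.05) = 0.322
- w = 0.322 × 0.0441 / (0.2059 + 0.322 × 0.0441) = 0.0142 / 0.2201 = 0.0645
- SE = √[0.95 / (800 × 0.2201)] = 0.073

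| ρ | Between-program slope | Spurious effect (w × slope) | Approximate rejection at two-sided 5% |
|---|---|---|---|
| 0 | 0 | 0 | 5% |
| 0.3 | 0.3 × 0.2236 / 0.21 = 0.319 | 0.021 SD | 6% |
| 0.7 | 0.7 × 0.2236 / 0.21 = 0.745 | 0.048 SD | 10% |

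The rejection rate is P(|Z + bias/SE| > 1.96). A simulation of essentially this setting (500 runs, ρ = 0.7) gave 0.050 SD and 11.6%, in line with the hand calculation.

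**Simulated range over all assumed settings.**

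| ρ | Spurious benefit | False-positive rate |
|---|---|---|
| 0 | about 0 SD | about 5% |
| 0.3 | 0.01 to 0.03 SD | 4 to 8% |
| 0.7 | 0.02 to 0.08 SD | 7 to 15% |

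**Harsher setting.** The size also depends on how widely review rates vary. With quality shifting the log-odds of review by 2 per SD, 20 programs, N = 400 and ρ = 0.7, a separate simulation reached 0.12 to 0.13 SD and about 23% rejection.

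**After the fix.** With the program mean of review in the model, bias was within about 0.01 SD of zero. In the hand case the SE grows by √(0.2201 / 0.2059) = 1.034, or 3.4%. Over the assumed settings it grows by 3 to 12%.

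**The case against.** **An article may leave covariates to the SAP.** The exact covariate list is properly deferred, and the article does not rule out program-level terms. But it does state the form of the model, the two levels of covariates and the random site effect. The point concerns that stated form.

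**The investigators know that programs matter.** The Discussion says program elements will be evaluated through the fidelity assessment, and the Program fidelity section leaves room to use those data. This stands, but neither statement ties program data to the Aim 3 model.

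**No correlation is shown.** This stands. A reader might infer that the Aim 3 result is confounded, or that better-resourced programs with lighter caseloads and more support will pass for a benefit of review. The article does not support that. It says nothing about caseload and review, all programs are trained, each has a point person, and the passage on high and low adoption concerns interview sampling, not team-lead review rates.

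**The bias is modest.** Also true. At correlation 0.3 or less it is hard to distinguish from none, and in the hand case at 0.7 it is smaller than one standard error (0.048 against 0.073). The simulations also omit repeated records and clinician covariates.

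**Change scores remove stable differences in level.** They do, so only program differences in trajectory can bias the result. Such differences remain plausible: admission criteria vary by program, and programs may anchor the survey baseline to different visits.

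**A within-program contrast is not clean either.** Correct. Clinicians within a program differ, and the in-app risk notifications prompt staff to look at the data of service users who endorse risk.

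**Conclusion.** The concern holds as a weakness in a stated model, not as a demonstrated bias. The planned review coefficient blends within-program and between-program contrasts, and the protocol's own account of the network gives reason to doubt the independence that a random site intercept requires. Retaining the clinician and service-user random effects would not cure this, because they do not remove confounding by program.

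The size rests on assumed values for the number of programs, ICC, spread of review rates and, above all, the correlation between program quality and review. It runs from nothing at correlation 0 to 0.02 to 0.08 SD at 0.7, and is larger only if review rates vary very widely between programs. A change is worthwhile because the remedy is cheap and the coefficient carries the central claim of Aim 3.

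**What to change.** In the Aim 3 part of the Data analysis section:

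1. Add each program's mean review rate to the Aim 3 models, or use program fixed effects. Where the exposure is the in-app query on impact on the treatment plan, use the program mean of that indicator.
2. Base the Aim 3 conclusion on the within-program coefficient.
3. Report the between-program coefficient separately, with adjustment for FEPS-FS as a sensitivity analysis, and say that it is not read as an effect of measurement-based care.
4. State that the within-program estimate is still an association, open to confounding by clinician and by risk notifications that prompt review.

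The cost is one covariate per model (or a set of program indicators) and a few sentences, with no new data. The standard error rises by about 3 to 12% under the assumptions above. It would rise more if review is mainly a program-level habit, because little within-program variation would then remain. In that case the data could say little about review apart from program, and the report should say so.

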To determine if implementation of the LHCN leads to an increase in the delivery of measurement-based care (Aim 2), providers will complete self-report questionnaires in the pre- and post-implementation period of the project. To examine adoption of a new technology in the EP program, we will compare providers with respect to their self-reported use of data to determine treatment choices at two timepoints: prior to Beehive implementation, and then after training in and use of Beehive. Pre- Beehive implementation surveys include Treatment Alliance and Use of Data in Care Planning in reference to specific service users. Providers will also complete the Comfort with Technology survey. The sampling frame for each site will consist of surveys about service users of currently enrolled EP providers, restricted to service users with at least six months under treatment and who had been seen in the preceding month. Beehive training materials will then be implemented consistently across participating EP programs; implementation efforts will highlight the utility of data to identify treatment goals and metrics of improvement during treatment planning and provide guidance on service user-centered ways to collaboratively review data and monitor progress during care. Then, in post-implementation, the same set of surveys are administered to EP programs who have implemented Beehive in their program for at least a year. The survey sampling strategy used in the pre-implementation period to select clinician-service user pairs will be repeated after Beehive has been implemented in the clinic for a full year, to ensure a valid pre/post comparison on this outcome. Due to expected turnover from the clinician side and discharge/exit from the program on the service user side, we will not be able to sample the same group from the pre-implementation period. However, there will most likely be some representation in the post-implementation period from respondents who participated in the first phase of surveys. Therefore, these are not completely independent samples, nor are they completely repeated samples.

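### Aim 3 lets the Schwarz criterion decide whether the clinician level stays in the model; keeping the design levels by rule is a cheap, minor-to-moderate improvement

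*Protocol article*

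**What the plan says.** All of this is in the Data analysis section of the protocol article, in the Aim 3 text.

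- **Structure.** The plan states that "there is nesting of measurements from service users, who are nested within clinicians within EP programs", and gives this as the reason for using generalized linear mixed models.
- **Random effects.** "Random effects will be specified for sites, with additional effects specified for clinician and service users", with the last two tied to their "contribution to the model fit, according to the Schwarz Information Criterion". The site effect is unconditional. No fallback, such as cluster-robust standard errors, is stated.
- **Records.** The dataset has "one record per service user per follow-up assessment timepoint", with outcomes taken "for each of the six-monthly assessment timepoints during the first 24 months", so up to four records per person (6, 12, 18 and 24 months).
- **Outcome scale.** "Continuous outcomes will be transformed into within-person change scores from the baseline assessment for each follow-up assessment".
- **Exposure.** For review of survey data, "this variable will be scored a 1 for a given service user in a given follow-up assessment if the treatment team lead reviewed" the completed surveys. The same section also speaks of clinician metrics aggregated over follow-up. A second exposure, reported impact on the treatment plan, varies over time within the service user. Outcome measures and instruments describes the treatment team lead as usually the primary clinician.

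**The concern.** Clinician and service user are levels of the design, not candidate predictors. The plan acknowledges them and then lets the data decide whether the model respects them. BIC admits a variance component only if it improves twice the log-likelihood by more than log(n), so modest but real clustering can be removed.

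Clinician is the level to watch, because the lead performs the review. If review habits differ between clinicians and outcomes also cluster by clinician, a model without the clinician effect treats correlated service users as independent and gives an exposure interval that is too narrow. Aim 3 asks whether measurement-based care is associated with significant improvement, so the cost would be too many false positives on that question.

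**Working it through.** **No figure to reproduce.** The article gives no ICC, clinician count, standard error or power for Aim 3. Its Sample size section gives 500 + 300 = 800 expected service users, based on intake estimates. The effect of the rule therefore has to be shown over a range of assumptions.

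**Service-user level.** Take equal variances σ² and a common correlation ρ between assessments. Two change scores of one person have covariance ρσ² − ρσ² − ρσ² + σ² = (1 − ρ)σ², and each has variance 2(1 − ρ)σ². Their correlation is (1 − ρ) / [2(1 − ρ)] = 0.5, whatever ρ is. BIC will see clustering this strong.

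**BIC threshold.** With 800 people and 4 follow-ups, n = 3,200 observations and log(3,200) = 8.07. With n = 20 sites, log(20) = 3.00. The article does not say which n applies, so both were run.

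**Simulation.** A balanced linear mixed model with a null exposure was fitted by maximum likelihood, with Wald intervals and 800 runs per setting. The Monte Carlo standard error of coverage is √(0.95 × 0.05 / 800) = 0.8 points. Each dataset was fitted with site only, site + clinician, site + user, and all three; the lowest BIC was selected. Only the total of 800 and the maximum of 4 follow-ups come from the article. Assumed inputs:

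- 20 sites, with 2, 5 or 10 clinicians per site (20 × 2 × 20 = 20 × 5 × 8 = 20 × 10 × 4 = 800 service users)
- 2 or 4 follow-ups
- site ICC 0.03; clinician ICC 0 to 0.10
- service-user variance share 0.45 (0 to 0.20 as a check)
- clinician share of the latent exposure 0.3, 0.7 or 1.0, where 1.0 means the clinician wholly sets it

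How often the clinician effect was dropped:

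| Clinician ICC | n = observations | n = sites |
|---|---|---|
| 0.01 | 96-99% | 79-92% |
| 0.02 | 82-96% | 53-81% |
| 0.05 | 26-75% | 7-38% |
| 0.10 | 1-12% | 0-3% |

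The service-user effect was dropped in 0% of runs at a variance share of 0.45 and in at most 0.1% at 0.20. At 0.10 it was dropped in 0% with 4 follow-ups and 33% with 2. Frequent dropping with 4 follow-ups needed a share of 0.05 or less.

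Coverage of the nominal 95% interval (n = observations):

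| Clinicians per site, follow-ups | Clinician share of exposure | Clinician ICC | All levels kept | BIC-selected | Loss (points) |
|---|---|---|---|---|---|
| 5, 4 | 0.7 | 0.02 | 94.1% | 93.9% | 0.2 |
| 5, 4 | 0.7 | 0.05 | 94.4% | 94.1% | 0.3 |
| 5, 4 | 1.0 | 0.02 | 95.0% | 92.9% | 2.1 |
| 5, 4 | 1.0 | 0.05 | 95.8% | 94.2% | 1.6 |
| 2, 4 | 1.0 | 0.02 | 94.6% | 91.0% | 3.6 |
| 2, 4 | 1.0 | 0.05 | 93.5% | 90.4% | 3.1 |

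Across all settings, coverage was 92.5-96.4% with all levels kept and 90.4-96.2% after selection. With a clinician share of 0.3 or 0.7 the loss was at most about 1 point.

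In the last row the clinician effect was dropped in 32.1% of runs, and coverage in those runs was 80.2%. The remaining 67.9% had coverage of (90.4 − 0.321 × 80.2) / 0.679 = 95.2%. The average therefore hides a minority of datasets in which the interval is clearly too narrow.

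**The case against.** The strongest reply is that BIC drops the clinician effect mainly when it is small, which is when dropping it costs little. At ICC 0.10 it was kept in at least 88% of runs. This stands, and it is why the loss is 0 to about 4 points and not more.

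Four stronger readings are tempting, but the article does not support them.

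- *The exposure is a clinician-level variable.* It is scored per service user per follow-up, and the second exposure varies over time. Review will cluster by clinician, but nothing says that it is constant within clinician. The settings with a clinician share of 1.0 are an extreme.
- *The service-user effect will be lost.* Dropping it with four records would give a design effect of 1 + 3 × 0.5 = 2.5 and, for an exposure constant over follow-up, a false-positive rate of 2 × P(Z > 1.96/√2.5) = 22%. The same correlation of 0.5 ensures that BIC keeps the effect, so the stated rule would practically never lead there for continuous change scores. Binary and count outcomes lack this built-in correlation and were not simulated.
- *The clinician effect will often be dropped.* That depends on an ICC, a clinician count and a choice of n that the article does not give.
- *Nesting in clinicians contradicts the expected turnover.* The remark "Due to expected turnover from the clinician side" explains why the Aim 2 provider surveys cannot resample the same group. It does not describe the Aim 3 dataset, and nothing bars linking a record to the lead at that time.

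The random-effects sentence is also compressed. The criterion could be meant to shape these effects and not to admit them. Admission is the more natural reading, and clearer wording would settle it.

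**Conclusion.** The point holds in a limited form. The article names clinician and service user as levels of the data and then, on the natural reading, makes their random effects depend on a fit criterion. This is a rule that the article states, not a detail left to a fuller plan. Its practical weight falls on the clinician effect.

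At worst, coverage falls to 90.4-91.0%, that is, 9.0-9.6% false positives against 5.4-6.5% with all levels kept. This takes 2 clinicians per site, an exposure wholly set by the clinician and an ICC of 0.02 to 0.05. With exposure varying within clinician, the loss is about 1 point or less.

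These sizes rest on assumed ICCs, site and clinician numbers, and on balanced data with continuous outcomes. Imputation and confounding were not modelled. It is a cheap improvement of minor to moderate importance and does not invalidate the Aim 3 analysis.

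**What to change.** Replace the random-effects sentence in Data analysis with wording such as: *Random intercepts for site, clinician and service user are retained in every Aim 3 model as levels of the design, even when a variance component is estimated near zero. The Schwarz criterion is used only to choose further terms, such as the within-person covariance pattern.*

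The cost is one sentence and slightly wider intervals. For the design levels, it also removes the question of which n enters the criterion.

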To determine the extent to which providers utilize the Beehive platform to deliver measurement-based care (Aim 2), we adopt two different approaches. First, we will examine whether a service user’s treatment team lead reviews completed surveys in Beehive, which is recorded by the application. During service user registration in Beehive, EP providers designate the service user’s treatment team lead, typically their primary clinician. Once a survey respondent completes a survey in Beehive, the data are immediately available to view in the Beehive dashboard. The Beehive survey reports will include a variable that shows whether or not each survey has been viewed by the service user’s treatment team lead (binary yes/no). Research staff will use this data to determine the degree to which providers are actively viewing data collected in Beehive.

To explore how Beehive data are used by those who frequently utilize the application, two types of in-app queries were developed: urgent clinical issues and data-use questions. Urgent clinical issues are a type of notification (in-app and email) in Beehive that encourages EP staff to review service user data. These notifications trigger if, during registration or survey completion, a service user endorses risk-to-self or risk-to-others on the Modified Colorado Symptom Index (MCSI) [26], the intent to stop taking their medication [27], or lack of a permanent address. Beehive displays urgent clinical issues on a dashboard widget and to resolve them, users must indicate how they used the data in care. Additionally, an in-app query is presented to the service user’s treatment team lead every ten visits to the service user’s data page. Data-use questions assess (1) if the data was reviewed during a session with the service user or support persons and, if yes, (2) how the data was used as part of care.

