To assess Aim 2, the adoption of Measurement-Based Care (MBC), we will first examine the degree of use of data in care between the pre- and post-implementation periods of the project. Before Beehive implementation in each EP program, providers complete pre-implementation surveys about their demographic information (age, sex, race, ethnicity) and professional characteristics (years of education, degree type) and complete questionnaires on their (1) beliefs about the utility of data in care planning and (2) skills in discussing data with service users. Compared to the pre-implementation period, we hypothesize that providers will report a change in the use of data to determine treatment choices after training and using the app for at least one year. Separate models will be fit for each of the primary and alternative operationalization of Beehive clinician-usage metrics as the exposure variable of interest. Adoption of data in care will also be measured by examination of whether a service user’s treatment team lead examined completed surveys from service users. To determine the degree to which providers are actively viewing data collected in Beehive, research staff will review the Beehive survey reports variable that shows whether or not each survey has been viewed by the service user’s treatment team lead (binary yes/no). We hypothesize that EPI-CAL treatment team leads will have viewed service user data collected through Beehive in at least 50% of cases. Lastly, we will examine whether the clinician reported that Beehive data impacted the treatment plan as assessed by the in-app queries periodically presented to EP provider users.

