#### Analysis of population and missing data

All EP program service users are eligible to participate in the study and complete surveys on Beehive. To address attrition in longitudinal survey completion and missing data, we will use multiple imputation to impute follow-up assessment scores and change scores based on them, as appropriate.

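### Aim 3's any-review exposure, aggregated over three follow-ups, mixes survey completion with clinician review, and it conflicts with the per-assessment scoring given beside it

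*Protocol article*

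**What the plan says.** All references are to the protocol article.

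- **Per-assessment scoring (Data analysis).** The review indicator is introduced follow-up by follow-up: "this variable will be scored a 1 for a given service user in a given follow-up assessment", on condition that the lead looked at that user's completed survey data.
- **Aggregated groups (Data analysis, next sentence).** The comparison groups use Beehive metrics "aggregated over the 6-, 12- and 18-month assessment period". The same sentence then names the main contrast, which concerns viewing by the lead: "and the primary analysis is based on a composite indicator for any review of the service".
- **Analysis dataset (Data analysis).** It holds "one record per service user per follow-up assessment timepoint". The models adjust for a small set of clinician and service-user covariates.
- **What can be viewed (Outcome measures and instruments).** Beehive records "whether or not each survey has been viewed by" the lead, and a survey becomes viewable once it has been completed.
- **Expected viewing (Data analysis, Aim 2).** Leads "will have viewed service user data collected through Beehive in at least 50% of cases".
- **Missing data (Analysis of population and missing data).** "we will use multiple imputation to impute follow-up assessment scores and change scores based on them, as appropriate". The exposure is not mentioned there.

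**The concern.** An indicator of whether something ever happened depends on how often it could have happened. Here the opportunities are completed survey timepoints, and they differ between service users. Someone who completes all three named follow-ups has three chances to be classed as reviewed. Someone who completes one has one chance, and someone who completes none has no chance. The aggregated definition has no denominator, and the section names no condition on the number of surveys available.

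The same section says that there is no group without Beehive, so Aim 3 rests on this contrast. If people who keep completing surveys also have a different prognosis, some of that difference will be credited to measurement-based care.

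The two scoring sentences also lead to different analyses. The per-assessment version avoids accumulation across timepoints but meets another problem. Where a follow-up survey was not completed and the outcome is imputed, there was nothing to view.

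**Working it through.** The plan states no effect size, power or retention figure for Aim 3, so it has no figure of its own to reproduce.

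**Step 1. Chance of being classed as reviewed (aggregated version).** Let k be the number of completed timepoints among 6, 12 and 18 months, and p the chance that the lead views the data at one completed timepoint. If views are independent across timepoints, P(any review) = 1 − (1 − p)^k. The value p = 0.50 is borrowed from the Aim 2 hypothesis, which is a minimum; the other values are assumed.

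| p | k = 0 | k = 1 | k = 2 | k = 3 |
|---|---|---|---|---|
| 0.20 | 0 | 0.20 | 0.36 | 0.49 |
| 0.35 | 0 | 0.35 | 0.58 | 0.73 |
| 0.50 | 0 | 0.50 | 0.75 | 0.875 |
| 0.70 | 0 | 0.70 | 0.91 | 0.97 |

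**Step 2. Conversion to MCSI points.** Assume p = 0.50, half of users with k = 1, half with k = 3, and no effect of review.

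- Share of three-timepoint completers among the reviewed: 0.875 / (0.875 + 0.50) = 0.636.
- Share among the not reviewed: 0.125 / (0.125 + 0.50) = 0.200.
- Difference: 0.436.
- Spurious difference at an assumed prognosis gap of 3 points: 0.436 × 3 = 1.3. At 2 points it is 0.9, and at 4 points 1.7.

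**Step 3. Simulation with no review effect.** It used 200,000 service users and three waves, with monotone retention of 0.60, 0.75 or 0.90 per wave. Mean review probability was 0.5, either constant or varying as Beta(5,5) or Beta(1,1). A latent factor raised retention and improved the outcome (correlation with the change score about −0.3). All of these inputs are assumptions.

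- Users ever reviewed looked better by 0.12 to 0.20 SD overall, and by 0.04 to 0.10 SD among users with at least one survey.
- Stratified by number completed, the difference was about 0 (within 0.01 SD either way).
- The indicator's correlation with number completed was 0.49 to 0.74. Where review propensity varied, its correlation with that propensity was 0.16 to 0.48.
- The share of completed surveys viewed was uncorrelated with the number completed (|r| below 0.005).

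**Step 4. Per-assessment version.** The indicator for one follow-up uses only that follow-up's surveys, so Step 1 does not apply across timepoints. For a follow-up with no completed survey and an imputed outcome, the indicator can only be 0 or undefined. Coding it 0 would classify the lead's behaviour where no review was possible.

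**The case against.** The strongest reply is that the per-assessment sentence, with one record per user per follow-up, is the operative definition. The word any would then mean any of the several surveys at one assessment, and nothing builds up across timepoints. That reading is possible and removes Steps 1 to 3. However, the sentence that names the primary analysis is the one that aggregates, so the text does not settle the matter.

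The gradient also depends on independence. If half of leads always review and half never do, P(any review) is 50% at k = 1, 2 and 3, and only users with no completed survey differ. Review by a designated lead may well cluster, so this stands as a limit on size. The 50% is a hypothesised minimum for undefined cases, not a stated rate per timepoint.

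The article is condensed, and the full covariate list and imputation details may be in an analysis plan that is not shown. Their absence is not the point here. The point is the exposure rule that the article itself states.

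A reader might infer several stronger things that the document does not support:

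- **That the exposure measures retention instead of clinician behaviour.** It mixes both. With 90% retention per wave and wide spread between leads, the two correlations were about equal (0.49 and 0.48).
- **That every imputed record is unexposed.** Under aggregation, a user reviewed at 6 months and missing at 12 stays in the reviewed group.
- **That the unexposed group becomes very small.** A 12.5% share needs everyone to complete all three timepoints, and then completion does not differ. In the Step 2 mix the share is (0.50 + 0.125) / 2 = 31%. Relative to an even split the standard error is √(0.25 / (0.6875 × 0.3125)) = 1.08 times as large.
- **That scores will be imputed after discharge.** The missing-data section does not say so.

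Functioning scales are rated by clinicians, so those outcomes can exist without a service-user survey. The time-varying analysis of impact on the treatment plan uses a different exposure.

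**Conclusion.** The concern holds for the aggregated any-review indicator, which the article names as primary. That indicator confounds survey completion with clinician review. The direction is mechanical unless the same leads always or never review. The size is not known from the document: 1.3 MCSI points (0.9 to 1.7) rests on an assumed 50% independent review probability, an assumed even split between one and three completed timepoints, and an assumed prognosis gap of 3 points (2 to 4). If completion is unrelated to prognosis, this bias does not arise.

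Under per-assessment scoring the accumulation problem disappears. What remains is the exposure of a follow-up with an imputed outcome and no completed survey. The two sentences need to be reconciled in either case.

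**What to change.** 1. Replace the two sentences with one exposure definition.
2. Define exposure only where at least one completed survey was available to view, either as a per-assessment indicator or as the share of available survey timepoints that the lead viewed.
3. Adjust for, or stratify by, the number of survey timepoints available. Report the unadjusted result as a sensitivity analysis, because earlier review may itself affect later completion.
4. State that exposure is not coded 0 when no survey existed, including for follow-ups with imputed outcomes.

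The change is to analysis wording only, since the viewed flag and the survey completion records are already in Beehive. It has two costs: service-user periods with no available survey leave the exposure contrast, and adjustment may remove any part of the effect that works through better engagement.
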